### Methods in analysis to handle protocol non-adherence and any statistical methods to handle missing data {20c}

To address protocol non-adherence, we will define the analysis populations as follows: the intention-to-treat (ITT) population will include all randomized participants who have at least one treatment record and will be used for analyzing the primary outcome. The per-protocol (PP) population will include only those participants who fully adhere to the study protocol without major deviations and will be used for analyzing the secondary outcomes. Experience indicates that dropouts are rare. If the proportion of missing data exceeds 10%, multiple imputation techniques will be employed to ensure the robustness of our study results.

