### Intervention description {11a}

After signing the informed consent, participants will be randomly allocated to either the PI group (intervention group) or the AT group (control group). Participants in the PI group will receive a subcutaneous injection of 140 mg (1 ml) of evolocumab (Rephatha®, Amgen Inc.) and orally take 20 mg of rosuvastatin (Crestor®, AstraZeneca Inc.) calcium tablets within 1 h of randomization. Starting from the following day, they will receive 20 mg of rosuvastatin calcium tablets orally every evening and 140 mg of evolocumab subcutaneously once every 2 weeks. Participants in the AT group will receive 20 mg of rosuvastatin calcium tablets orally within 1 h of randomization. Starting from the next day, they will continue to orally receive 20 mg of rosuvastatin calcium tablets orally every evening.

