### Criteria for discontinuing or modifying allocated interventions {11b}

Participants are allowed to withdraw from the study at any time due to various reasons, including failure to meet the inclusion criteria, inability to continue with the intervention treatment, or participant request.

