## Assignment of interventions: blinding

### Who will be blinded {17a}

Researchers responsible for data collection and outcome analysis will be blinded to group assignments until after data analysis is completed, as they will not be involved in participant assignment or intervention implementation.

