### Procedure for unblinding if needed {17b}

Not applicable to study; the design is open label, so unblinding will not occur.

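### The primary-outcome population labelled ITT requires a treatment record, so it is a modified ITT set whose exclusions can depend on known allocation; the likely effect is small

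*Protocol article*

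**What the plan says.** All references are to the protocol article.

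- Section {20c} defines the population: "the intention-to-treat (ITT) population will include all randomized participants who have at least one treatment record". It assigns this population to the primary outcome. It does not define a treatment record.
- Section {17b} on unblinding states: "Not applicable to study; the design is open label, so unblinding will not occur". Section {17a} limits blinding to other staff: "Researchers responsible for data collection and outcome analysis will be blinded to group assignments until after data analysis is completed".
- Section {11a} sets the first treatment after allocation. For the control arm: "Participants in the AT group will receive 20 mg of rosuvastatin calcium tablets orally within 1 h of randomization". In the PI group, evolocumab and rosuvastatin are given in the same one-hour window.
- Section {11b} on discontinuation allows early exit: "Participants are allowed to withdraw from the study at any time due to various reasons, including failure to meet the inclusion criteria". Participant request is another listed reason.
- Section {26b} says the consent form asks for permission to go on using data after withdrawal.
- Section {20a} gives a different and stricter rule: only strict adherers are analysed and missing data are left out. It conflicts with {20c}.

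**The concern.** Intention-to-treat means that everyone randomised is analysed as randomised. The rule in {20c} adds a condition that can be met only after randomisation. In a double-blind trial, leaving out never-dosed participants can be defended because nobody knows the arm when the decision not to dose is made. That defence is not available here: participant and treating staff know the arm before the first dose.

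Someone can therefore learn the allocation, leave or be withdrawn before any dose, and disappear from the primary comparison. Blinded NIHSS rating does not help, because the person is not in the set to be rated. The comparison would still be reported as intention-to-treat.

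The conflict between {20a} and {20c} is a separate and larger problem. Settling it in favour of {20c} would leave this flaw in place, so the two should be dealt with together.

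**Working it through.** **1. Who is in the set.** Someone who leaves after a first dose has a treatment record and stays in the {20c} set. Someone who leaves before any dose has none and is out, on the natural reading of the term. No other section brings that person back. Section {20a} is stricter, and the multiple imputation rule in {20c} does not redefine the population.

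**2. Planning figures (section {14}).** END is assumed at 33.3% in AT and 13.6% in PI, a difference of 19.7 points; two-sided α is 0.05, power 80%, with 70 per group before loss.
- The usual pooled-variance formula for two proportions gives 72 per group and the unpooled one 69, so 70 is reproduced to within two patients.
- Loss of 10%: 70 / 0.9 = 77.8, so 78 per group and 156 in total, as stated.
- Expected AT events: 78 × 0.333 ≈ 26. Each participant dropped is 1/156 = 0.64% of the trial.

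**3. Effect on the planned difference.** The document gives no rate of never-treated participants, so the count is assumed: four in AT, none in PI.
- All four would have had END: (26 − 4)/74 = 29.7%; difference 29.7 − 13.6 = 16.1 points.
- None would have had END: 26/74 = 35.1%; difference 35.1 − 13.6 = 21.5 points.
- The four have average risk: (26 − 4 × 0.333)/74 = 33.3%; difference 19.7 points, no bias.

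**4. Effect on type I error.** Assume no true effect, 33.3% END in both arms, 78 in PI, and k of 78 AT participants dropped, of whom a fraction q would have had END. The retained AT rate is (78 × 0.333 − kq)/(78 − k). A two-sided 5% test with pooled standard error then gives:

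| k dropped (AT only) | q = 0: bias, type I error | q = 1: bias, type I error |
|---|---|---|
| 2 | +0.9 points, 0.052 | −1.8 points, 0.056 |
| 4 | +1.8 points, 0.056 | −3.6 points, 0.076 |
| 8 | +3.8 points, 0.077 | −7.6 points, 0.172 |

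Bias is AT minus PI, so a positive sign favours the PI group. For k = 4 and q = 0.5 the bias is −0.9 points and the type I error 0.052.

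**5. Power if everyone is kept.** Suppose k of 78 PI participants are never dosed and have the control END rate (an assumption). The PI rate becomes (0.136 × (78 − k) + 0.333k)/78. Power at 78 per group is 0.834 for k = 0, 0.811 for k = 2, 0.786 for k = 4 and 0.733 for k = 8. The target of 156 is unchanged.

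**The case against.** The strongest reply is that the rule will hardly ever operate. Treatment is due within an hour of randomisation, in hospital, in both arms. Both arms include a statin, which section {6b} describes as established treatment for these patients. Section {20c} expects few dropouts. All of this stands, and it limits the size of the point.

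A reader might infer more than the documents support, in three ways.

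- **That exclusion follows the early clinical course.** END is counted from 24 h to 7 days after onset, while participants are enrolled within 24 h of onset and dosed within an hour of randomisation. Most exclusions would be settled before the END window opens. The plausible route is reaction to the allocation, and nothing in the document ties that to END risk.
- **That the filter works harder on AT than on PI.** A PI participant could refuse the injection, take the tablet and keep a record, while an AT participant who refuses the tablet has none. This compares refusal of part of the treatment with refusal of all of it. Participants who refuse everything are filtered alike in both arms, and the PI participant who takes only the tablet would also be kept under true ITT.
- **That 16.1 to 21.5 points is an estimate.** It rests on four exclusions in one arm, none in the other, and all or none of the four with END. The document supports none of these figures.

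It is also fair to say that a treatment record is undefined, and that changing the definition does not by itself produce a day-7 score for someone who withdraws consent to follow-up. The consent wording in {26b} covers continued use of data; it does not secure a later assessment.

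The definition itself survives these replies. If exclusions are few, keeping those people costs almost nothing; if they are not few, the rule does harm.

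**Conclusion.** The point holds as one of definition: the primary-outcome set is modified ITT under an ITT label, and because the arm is known before first treatment the exclusion can depend on allocation. This rests on reading a treatment record as evidence of at least one dose, which is the likely meaning but is not stated.

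The documents do not show that the primary comparison will be materially biased. The number excluded is probably small, and the bias modest and of unknown direction. It is zero if those excluded have the average risk of their arm. With two AT-only exclusions, type I error stays between 0.050 and 0.056 for any prognosis considered; marked distortion needs more exclusions, in one arm only, with extreme prognosis. The rule should be corrected, but it does not call the design or the sample size into question.

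**What to change.** Make the change when sections {20a} and {20c} are reconciled:

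1. Define the primary set as all randomised participants, analysed in the arm assigned, regardless of treatment received.
2. Assess day-7 END in everyone who has not withdrawn consent to follow-up, including those never dosed.
3. Keep participants without a day-7 assessment in the set and treat them as missing outcome data, for example by multiple imputation, which {20c} already names. That section invokes it only when more than 10% of data are missing, and {20a} excludes missing data, so the text must say that it applies to these participants.
4. Rename the present set modified ITT, define what counts as a treatment record, and keep it for a sensitivity analysis.

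The cost is a short change of text and the already scheduled day-7 assessment for a few untreated participants. The target of 156 stays. The estimate may be slightly less favourable, because never-dosed PI participants dilute the contrast: with four of them at the control END rate, power at 78 per group falls from 0.834 to 0.786.

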### Outcomes {12}

The primary outcome of this study will be the END within 7 days. END will be defined as a 2-point increase in the NIHSS score or a 1-point increase in motor function (specifically NIHSS Items 5, 6, and 7) within 24 h to 7 days of AIS onset. To address the potential impact of END severity on the reliability of the primary outcome, we will conduct a sensitivity analysis using a higher threshold: a 4-point worsening in the NIHSS or a 2-point increase in motor function, which will be classified as severe END.

The secondary outcomes of the study will include:Evaluation the rate of good prognosis at 30 and 90 days. Good prognosis will be defined as a modified Rankin Scale (mRS) score of 2 or lower, which indicates either no disability or minor disabilityAssessment of the recurrence rate of symptomatic cardiovascular and cerebrovascular events within 90 daysAnalysis of changes in blood biochemical indices (including liver function, renal function, lipid profile, etc.) before and after treatment, measured at baseline, 7 days, 30 days, and 90 daysExamination of changes in inflammatory factors (interleukin-6, IL-6; interleukin-8, IL-8; tumor necrosis factor-alpha, TNF-α) before and after treatment, assessed at baseline and 7 days

Safety outcomes will be documented by recording the types and frequencies of all adverse events and abnormalities in laboratory tests throughout the study duration. Safety evaluations will include assessments of the patients’ general condition, vital signs, blood routine tests, blood biochemistry, liver and kidney function, coagulation function, and neuroimaging examinations. All participants will undergo assessments before treatment initiation and at the initial treatment milestones of 30 days and 90 days.

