### Follow-up

The follow-up period will start on day 8 after enrollment and continue until day 90, with evaluations on days 30 and 90. Assessments will include concomitant medications, adverse events, physical examinations, laboratory tests, NIHSS and mRS scores, and the occurrence of any recurrent cardiovascular or cerebrovascular events. If a participant experiences an endpoint event (recurrent cardiovascular or cerebrovascular event) during treatment or follow-up, the clinical study will be terminated, and active management will be initiated.

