## Statistical methods

### Statistical methods for primary and secondary outcomes {20a}

Once all participants have completed their assessments, data analysis will commence. To reduce bias, the data analyst will remain blinded during the analysis process. Only participants who strictly adhere to the intervention protocol will be included in the analysis. Data that are missing or deviate from the protocol will be excluded from the analysis.

The primary and secondary outcomes will be combined as dependent variables in the generalized linear model (GLM). First, a univariate analysis of the treatment groups will be performed to determine the unadjusted risk ratio (RR) and odds ratio (OR), along with a 95% confidence interval (CI). Next, continuous variables like the NIHSS score at admission, mRS score, and age will serve as covariates. Categorical variables such as sex, hypertension, diabetes, and prior strokes will be included as factors in the GLM to reduce variance error. If the outcomes show statistical significance for the main effects, interaction effects will be used to assess differences between the groups. Changes in blood biochemical indices will be analyzed using repeated measures ANOVA or mixed-effects models, accounting for measurements taken at baseline, 7 days, 30 days, and 90 days. Changes in inflammatory factors (IL-6, IL-8, TNF-α) from baseline to 7 days will be evaluated using paired *t*-tests or Wilcoxon signed-rank tests, based on data distribution. Sensitivity analysis will use the criterion for severe END, defined as either a 4-point increase in NIHSS or a 2-point worsening in motor function based on a higher threshold. All analyses will be conducted using SPSS (IBM Corp., Armonk, NY, USA), with a significance threshold of *α* = 0.05.

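### The per-protocol set is the only analysis set for the secondary outcomes, so the 30- and 90-day mRS and 90-day recurrence comparisons can be biased by selection after randomisation

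*Protocol article*

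**What the plan says.** Section {20c} of the protocol article defines two populations and gives each a task. The ITT population consists of "all randomized participants who have at least one treatment record and will be used for analyzing the primary outcome". The per-protocol population is limited to those who "fully adhere to the study protocol without major deviations and will be used for analyzing the secondary outcomes". No secondary outcome is exempted, and no second analysis set is named for any of them.

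Section {20a} does not soften this. It states, "Only participants who strictly adhere to the intervention protocol will be included in the analysis", and then, "Data that are missing or deviate from the protocol will be excluded from the analysis".

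Outcomes {12} lists four secondary items. The first is "Evaluation the rate of good prognosis at 30 and 90 days", defined as mRS 2 or lower. The others are symptomatic cardiovascular and cerebrovascular recurrence within 90 days, changes in blood biochemistry, and changes in inflammatory factors.

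Three other statements bear on who might leave the per-protocol set:
- Section {17b}: "the design is open label, so unblinding will not occur".
- Section {11a}: both groups take rosuvastatin every evening, and the PI group also receives "140 mg of evolocumab subcutaneously once every 2 weeks".
- Follow-up section: if a recurrent vascular event occurs "during treatment or follow-up, the clinical study will be terminated, and active management will be initiated".

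**The concern.** Randomisation makes the arms comparable as allocated. A set defined by adherence over 90 days is formed afterwards and can differ between arms in ways related to prognosis. For a superiority question, that makes per-protocol a supportive analysis and a poor choice as the only one.

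Three features of this trial make unequal selection possible. The PI group has an additional two-weekly injection, so it has more ways to fall short of full adherence. Allocation is known to participants and treating staff, so non-adherence and withdrawal can depend on it. A recurrent event is itself a secondary outcome and also ends the participant's study, yet the article does not say whether that participant stays in the per-protocol set or is still scored on the mRS at day 90.

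At stake are the conclusions on disability and recurrence, the results closest to the improved overall prognosis that the Discussion gives as a goal. Under {20c} they would also describe different patients from the primary result.

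**Working it through.** **The plan's own figure.** The sample size concerns END only: 70 per group, and 70 / 0.9 = 77.8, rounded up to 78, or 156 in total. This point does not change it. The article gives no planning rate for mRS or recurrence, so there is no secondary-outcome figure to reproduce.

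**Inputs for an illustration**
- 78 per arm, 1:1, two-sided α 0.05: sections {14} and {16a}.
- Bad-outcome rate p, the same in both arms (no true effect): 0.333 and (0.333 + 0.136) / 2 = 0.2345. These are borrowed from the END rates in {14}. Using them for the secondary outcomes is an assumption.
- Fraction r of bad-outcome patients removed by the per-protocol filter: assumed.

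**Formula.** After removal, an arm's apparent bad-outcome rate is p(1 − r) / (1 − pr). If only one arm is affected, RR = (1 − r) / (1 − pr).

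Example, r = 0.20 and p = 0.333: 0.8 × 0.333 / (1 − 0.0666) = 0.2664 / 0.9334 = 0.285, and 0.285 / 0.333 = 0.86. With p = 0.2345: 0.8 / (1 − 0.0469) = 0.84.

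**Error rate.** Simulated with 400,000 trials per scenario, pooled z-test, two-sided 0.05:

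| Removal of bad-outcome patients | Patients lost from the affected arm (78pr) | RR | Two-sided error |
|---|---|---|---|
| Equal in both arms (20/20 or 30/30) | not applicable | 1.00 | about 5% |
| 10%, one arm | 1.8-2.6 | 0.92-0.93 | about 6% |
| 20% versus 10% | 3.7-5.2 versus 1.8-2.6 | 0.91-0.92 | about 6% |
| 20%, one arm | 3.7-5.2 | 0.84-0.86 | about 9-10% |
| 30%, one arm | 5.5-7.8 | 0.75-0.78 | about 14-17% |

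The false advantage goes to the arm that loses the patients. For a rarer outcome (assumed rate 5% to 10%, as recurrence might be), 20% one-sided removal gives about 5.6% to 6.7%.

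**A second illustration, with exclusions in both arms.** Assume 60% good prognosis in each arm and 5% of the AT group excluded.
- If 10% of the PI group is excluded and 30% of all excluded patients have a good prognosis: (0.60 − 0.10 × 0.3) / 0.90 = 0.633 against (0.60 − 0.05 × 0.3) / 0.95 = 0.616. The spurious difference is 1.8 points before rounding, and the error is 5.5%.
- If 15% of the PI group is excluded and no excluded patient has a good prognosis: 0.60 / 0.85 = 0.706 against 0.60 / 0.95 = 0.632. The difference is 7.4 points and the error 15.5%.
- If exclusion is unrelated to prognosis, the bias is zero.

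**The case against.** The strongest reply is that the harm is assumed. The removal fractions and outcome rates above are not the protocol's figures for these outcomes. Equal removal, or removal unrelated to prognosis, leaves no bias. Section {20c} expects dropouts to be rare, and {11c} gives every participant reminders and weekly adherence calls. All of this stands as a limit on the size. It does not justify per-protocol as the only analysis: rare dropout is not the same as full adherence over 90 days, and the additional injections fall on one arm.

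A reader might infer that patients who deteriorate, die, have an event or have an adverse reaction will be removed, so that the comparison is of selected survivors. The documents do not say this. Nothing classes any of these as a major deviation, and ending the study after a recurrent event is a step the protocol itself prescribes. The supported statement is narrower: the article leaves open whether such participants stay in the set.

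A reader might also infer that safety is affected. It is not: {12} lists safety apart from the secondary outcomes, and {20c} does not assign it to the per-protocol set.

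Finally, an on-treatment analysis is easier to defend for the laboratory changes than for mRS or recurrence. That stands too, and the fix reflects it.

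**Conclusion.** The point holds for the secondary outcomes, with most force for mRS at 30 and 90 days and recurrence at 90 days. Section {20c} makes a set chosen after randomisation their only basis, and {20a} reinforces the restriction. This is a stated choice, so it cannot be treated as a detail left to an analysis plan.

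The direction and size of any bias are unknown. On the borrowed rates, the illustrated error runs from about 5%, when removal is equal, to 14-17%, when 30% of bad-outcome patients are lost from one arm only. These are scenarios and not estimates for this trial. The sentence in {20c} does not touch the primary outcome. The conflict between {20a} and the ITT analysis of END is a related but separate matter.

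**What to change.** In {20c}, and consistently in {20a}, state that:
- the secondary efficacy outcomes, at least mRS at 30 and 90 days and recurrence within 90 days, are analysed in all randomised participants as allocated;
- participants with a recurrent event stay in that analysis;
- the per-protocol analysis of these outcomes is supportive.

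The cost is wording only, with no additional patients, and the change should be made before the data are analysed. If the laboratory outcomes are moved to the same set, non-adherent participants may slightly dilute the biomarker effects. Keeping a supportive per-protocol analysis alongside answers that.

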### Sample size {14}

This study is a randomized controlled trial with the intervention group as the PI group and the control group as the AT group. The study involves AIS patients with a confirmed history of CHD, and the primary outcome is the END in the two groups.

Based on our retrospective observation of 21 AIS patients with a history of CHD and no prior use of PCSK9 inhibitors, hospitalized at the First Affiliated Hospital of Dalian Medical University from April 2022 to June 2023, a total of 7 patients exhibited END within 24 h to 7 days of disease onset, accounting for 33.3%. During the same period, among 22 AIS patients with a history of CHD who were treated with PCSK9 inhibitors within 24 h of onset, 3 patients experienced END, accounting for 13.6%. Assuming the incidence of END in the intervention and control groups are 13.6% and 33.3%, respectively, with a two-sided α level of 0.05 and 80% power, we used the PASS software version 15 (NCSS, LCC, Taiwan 2017) to calculate the sample size. Each group requires 70 patients. Considering a 10% loss to follow-up, both groups will need 78 patients, making a total of at least 156 patients across both groups. The sample size calculation formula is as follows:$$n=2({Z}_{\alpha /2}+{Z}_{\beta }{)}^{2}\cdot p(1-p)\div (\delta {)}^{2}$$where:

*n* is the sample size per group.

*Z*_α_/2 is the critical value for a two-sided significance level (1.96 for *α* = 0.05).

Z_*β*_ is the critical value for power (0.84 for 80% power).

*p* is the estimated overall incidence rate.

*δ* is the expected difference between the two groups.

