## Assignment of interventions: allocation

### Sequence generation {16a}

The allocation sequence for this study will be generated using computer-generated random numbers. The randomization will be stratified by gender. To reduce the predictability of the sequence, blocked randomization will be used to ensure a 1:1 ratio between the PI group (PCSK9 inhibitor with statin) and the AT group (statin monotherapy). Details of the block sizes and the randomization process will be documented separately and will remain unavailable to those who enroll participants or assign interventions.

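### The 10% switch for multiple imputation lets up to 15 of 156 participants drop out of the END analysis, and changes the method at the 16th, for reasons unrelated to bias

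*Protocol article*

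**What the plan says.** Three statements in the protocol article bear on missing END.

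- **Missing data and non-adherence {20c}.** The primary outcome is assigned to an intention-to-treat population: everyone randomised who has at least one treatment record. Dropouts are described as rare, without a figure. The rule then reads: "If the proportion of missing data exceeds 10%, multiple imputation techniques will be employed to ensure the robustness of our study results". The section does not say what happens at or below 10%, or whether the 10% counts participants, END values or all data items.
- **Statistical methods {20a}.** "Data that are missing or deviate from the protocol will be excluded from the analysis". This sentence carries no threshold.
- **Sample size {14}.** "Considering a 10% loss to follow-up, both groups will need 78 patients, making a total of at least 156 patients across both groups".

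The only sensitivity analysis named, in Outcomes {12} and again in {20a}, is the higher threshold for severe END. It concerns the definition of the endpoint, not missing values.

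**The concern.** Whether dropping participants biases a comparison depends on why they are missing and how that relates to outcome and arm. The proportion missing does not settle this. A rule keyed to the proportion therefore turns imputation off without asking the question that matters, and makes the primary method depend on a single record near the threshold. It also sits badly with an intention-to-treat population, because members of that population without an END assessment are removed.

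Outcome-related missingness is conceivable here. The design is open label ({17b}). The Follow-up section says that a participant's study ends on a recurrent cardiovascular or cerebrovascular event, during treatment as well as follow-up, while the Treatment section places the primary assessment on day 7. An early recurrence could thus remove a participant who had deteriorated. At stake is whether a nominally significant END result would stand once the missing participants are accounted for.

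**Working it through.** **Inputs.** From Sample size {14}: END rates of 13.6% (PI) and 33.3% (AT), a 5% two-sided test, 80% power, 70 evaluable participants per group, and 78 per group after 10% loss. Allocation is 1:1 ({16a}). The trigger is strictly more than 10% ({20c}).

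**1. The plan's own figures.** The printed formula, with p = (0.136 + 0.333)/2 = 0.2345 and δ = 0.333 − 0.136 = 0.197:

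n = 2 × (1.96 + 0.84)² × 0.2345 × 0.7655 / 0.197² = 72.5, so 73 per group.

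The standard two-proportion formula gives 72 (pooled variance) or 69 (unpooled), so 70 is reproduced to within 2. The loss allowance matches exactly: 70/0.9 = 77.8, so 78 per group and 156 in total.

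**2. Where the switch falls.** 10% of 156 is 15.6.

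- 15/156 = 9.6%: not above 10%, so excluded.
- 16/156 = 10.3%: above 10%, so imputed.
- Planned loss in whole participants: (78 − 70) × 2 = 16.

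So 15 is the most that can be dropped without imputation, and the planned loss falls just on the other side.

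**3. What 15 exclusions could hide.** Assume that 8 AT and 7 PI participants are missing and that the design rates hold among those observed: 0.333 × 70 = 23.3, taken as 23, and 0.136 × 71 = 9.7, taken as 10. The missing outcomes are then filled in under stated assumptions. The p-values are from Pearson chi-square without continuity correction.

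| Missing participants with END | AT | PI | p |
|---|---|---|---|
| Complete case (all 15 excluded) | 23/70 (32.9%) | 10/71 (14.1%) | 0.0085 |
| All, both arms | 31/78 (39.7%) | 17/78 (21.8%) | 0.015 |
| None, both arms | 23/78 (29.5%) | 10/78 (12.8%) | 0.011 |
| 0 of 8 AT, 2 of 7 PI | 23/78 (29.5%) | 12/78 (15.4%) | 0.035 |
| 0 of 8 AT, 3 of 7 PI | 23/78 (29.5%) | 13/78 (16.7%) | 0.057 |
| 3 of 8 AT, 5 of 7 PI | 26/78 (33.3%) | 15/78 (19.2%) | 0.045 |
| 3 of 8 AT, 6 of 7 PI | 26/78 (33.3%) | 16/78 (20.5%) | 0.071 |
| 3 of 8 AT, 7 of 7 PI | 26/78 (33.3%) | 17/78 (21.8%) | 0.107 |
| 0 of 8 AT, 7 of 7 PI (worst case) | 23/78 (29.5%) | 17/78 (21.8%) | 0.27 |

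Fisher's exact test crosses 0.05 one participant sooner: p=0.054 with 0 of 8 AT and 2 of 7 PI, and p=0.068 with 3 of 8 AT and 5 of 7 PI.

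**4. Other starting points.** If all 15 missing are in PI (complete case 26/78 against 9/63, p=0.009), significance is lost once 7 of the 15 had END (26/78 against 16/78, p=0.071). A weaker observed result of 23/70 against 13/71 starts at p=0.048 and has almost no reserve.

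**The case against.** **The planned loss would trigger imputation.** A reader might infer that the threshold equals the planned loss, so that a trial running to plan never imputes. The documents do not support that: the allowance is 16 whole participants, or 10.3%, just above the trigger. What stands is that the switch lies within one participant of the planned loss.

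**The 10% covers 90 days; END is assessed by day 7.** Nothing in the article shows that 15 END values will be missing, and {20c} calls dropouts rare. This stands, and 15 is an upper bound, not a forecast. It does not rescue the rule: with fewer END values missing the trigger does not fire, and those that are missing are excluded.

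**The damaging scenarios are one-sided.** If worsening leads to missing data equally in both arms, the result holds (p=0.015 with END in every missing participant). Having 0 of 8 AT with END is itself unlikely at the design rate, about 0.667⁸ = 4%. This stands and limits the size of the concern.

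**The result does not reverse.** A reader might also infer that the dropped participants could turn the finding round. At the design rates they cannot: PI stays lower even in the worst case. What can be lost is nominal significance.

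**The detail may be in an analysis plan.** Imputation variables and sensitivity analyses often are, and their absence alone would be no finding. But the exclusion sentence and the trigger are stated here, and they are what needs changing. If {20a} governs alone, missing data are dropped at every level, so the two sections need reconciling in any case.

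**Conclusion.** The concern holds in limited form. As written, the two rules allow up to 15 of 156 participants to be excluded from an analysis labelled intention-to-treat, with the method changing at the 16th and no stated check on the effect of missing END. The choice rests on a quantity that says nothing about bias.

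The numerical exposure is conditional. It assumes that the 10% counts participants, that the design rates hold among those observed, and that as many as 15 END values are missing, which a 7-day endpoint may not approach. Under those assumptions, p moves from 0.0085 to 0.057 or above only when END among the missing is strongly unbalanced against PI, with a worst case of p=0.27. If missing participants resemble observed ones, the conclusion stands.

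**What to change.** 1. Delete the 10% trigger in {20c}.
2. Reconcile the exclusion of missing data in {20a} with the intention-to-treat population that {20c} assigns to the primary outcome.
3. State one missing-data rule for END and mRS that applies whenever any value is missing: multiple imputation using arm, sex, age, baseline NIHSS and the post-baseline data already collected (recurrent events, day-30 NIHSS and mRS). Classify deaths by a pre-stated endpoint rule and do not impute them.
4. Add a tipping-point analysis that varies the END rate among missing participants separately by arm. This step and step 2 carry most of the benefit, because imputation under missing-at-random does not by itself address missingness that depends on the outcome.

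The cost is revised wording, a few hours of programming and possibly slightly wider intervals. The change should be made before outcome data are seen.
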